**11. REFERENCES**

1. **INTRODUCTION**

Chronic obstructive pulmonary disease (COPD) is the 4th leading cause of death globally. In the UK, over a million people are diagnosed with COPD and an estimated further 2 million are affected . COPD is frequently associated with co-morbidities such as cardiovascular disease, renal insufficiency, depression and osteoporosis, leading to the widely accepted view that COPD is a complex multi-system disorder . Funding bodies including MRC have highlighted the need to determine new therapeutic strategies, including the extra pulmonary manifestations of COPD.

**1.1 BACKGROUND & RATIONALE**

Early studies of cognitive performance in COPD tended to focus on factors associated with functional neuronal impairment, namely hypoxaemia, but cognitive impairment is present in the absence of hypoxaemia and explains only a small proportion of the variance in cognitive ability in those patients with COPD who are hypoxaemic . Two recent studies suggest that it is occult cerebrovascular damage that plays a key role in brain damage and dysfunction in COPD. In the first study, we examined brain pathology in patients with stable COPD using MRI techniques to provide sensitive measures of white matter microstructure and grey functional activation. This showed widespread damage to white matter integrity and disturbance in functional activation of grey matter consistent with microvascular pathology . The second study, a European community cohort, suggests that obstructive lung disease is related to an increased risk of the developing of cerebral microbleeds (a marker of cumulative small vessel damage) .

Other neuroimaging studies relevant to brain pathology in COPD are mixed. Smoking has been shown to be associated with cerebral atrophy and reduced frontal grey matter density . However large population studies suggest that factors other than smoking are involved since impaired lung function is associated with cerebral white matter lesions independent of smoking and in non-smokers . Studies in well characterised patients with COPD are lacking, one study of male patients with “chronic respiratory disease” found them to have increased white matter lesions and cerebral atrophy , in contrast a small study comparing COPD patients with and without hypoxaemia showed not difference in brain volume or white matter lesions . Therefore questions remain about the precise contribution of smoking, impact on cognitive function and underlying pathophysiological mechanisms of brain pathology in COPD .

There is a high prevalence of traditional cardiovascular risk factors in patients with COPD including smoking, reduced physical activity and low socio-economic status. However, numerous studies have shown that airflow limitation is an independent risk factor for cardiovascular disease . Patients with COPD are at a significantly increased risk of cardiac events and stroke particularly in early disease and it is cardiovascular, not respiratory disease that is the leading cause of death . This evidence points to a potential 'COPD specific effect' that contributes to the increased vascular comorbidities.

Arterial stiffness is a non-invasive measure of vascular function and accurately predicts cardiovascular and cerebrovascular events. In addition, arterial stiffness is thought to contribute directly to end-organ vascular damage through reduced vessel compliance, excessive pressure pulsatility resulting in vascular remodelling and impaired blood flow . There is evidence of increased aortic stiffness in COPD, independent of smoking, which also relates to degree of airflow limitation and percent emphysema on thoracic CT . It has been suggested that arterial stiffness in COPD may be due to increased susceptibility to degradation of connective tissue or accelerated aging. These factors are also implicated in the development of emphysema suggesting a potential shared pathophysiology between pulmonary and vascular disease in COPD .

A recent comprehensive review of vascular disease in COPD presents several plausible mechanisms including systemic inflammation (IL-6, CRP), oxidative stress (through activation of matrix metalloproteinases), physiological stress (hypoxia, sympathetic nervous system activation), arterial stiffness, accelerated aging and protease/antiprotease inbalance. It is argued that many of these pathways are abnormal in COPD, independently predict cardiovascular disease, e.g. through atherosclerosis formation or vascular damage and also show direct pathophysiological links to the development of emphysema .

Cognitive impairment is a known consequence of cerebral small-vessel disease. Moderate to severe cognitive impairment has been shown in up to 60% of certain individuals with COPD , which may predict death and is likely to profoundly influence an individual’s ability to manage their disease . Therefore understanding the relationship between cerebrovascular disease and cognitive impairment in COPD is a research priority.

In addition to cerebral small vessel damage and cognitive dysfunction, other organs such as the heart, kidneys, and retinal are likely to be susceptible to small-vessel damage in COPD. Several large population studies have shown that COPD is a significant independent risk factor for myocardial infarction, with the effect most marked in early, mild disease and that people diagnosed and treated COPD are at increased risk for hospitalizations and deaths due to cardiovascular diseases . Acute exacerbations of COPD are inflammatory episodes associated with platelet activation, troponin rise and subsequent increased cardiovascular events . Left ventricular mass predicts heart failure and cardiovascular mortality and has been found to be increased in COPD and associated with pulmonary hyperinflation . A small exploratory study suggests that occult myocardial infarction may be responsible for delayed cardiac MR enhancement in COPD , another suggests right ventricular hypertrophy on cardiac MR is and early sign of RV overload . Finally percentage of emphysema and lung function have been found to be inversely associated with left ventricular filling, reduced stroke volume and cardiac output with preservation of ejection fraction .

Chronic renal failure is highly prevalent in elderly patients with COPD and associated with systemic inflammation but is a relatively understudied co-morbidity. Micro-albuminuria has been shown to be an independent predictor of future cardiovascular events and a marker of vascular endothelial dysfunction . To our knowledge, retinal vessels have not been extensively investigated in patients with COPD. Retinal photography is a sensitive and precise method of assessing retinal microvascular signs and is thought to be a potential marker for concomitant cerebral microangiopathy. Population based studies indicate that retinal microvascular changes, when defined from photographs, are associated with stroke independent of hypertension may be useful for studying subclinical cerebrovascular disease .

We propose to compare non-invasive MR brain imaging of white matter microstructure (diffusion tensor), cerebral perfusion (arterial spin labelling) and accumulated cerebral small vessel disease (cerebral microbleeds), in COPD patients to smokers without COPD.

This will also be the first study to explore mechanisms of cerebral small vessel disease in COPD by looking for associations between arterial stiffness, end organ vascular damage and cognitive function.

This research will provide essential data required to fund longitudinal and intervention studies designed to prevent vascular manifestations and the associated morbidity and mortality in COPD.

1. **STUDY HYPOTHESIS & OBJECTIVES**

Hypothesis:

1. COPD is associated with cerebral small vessel disease independent of smoking.
2. Cerebral small vessel disease in COPD is associated with aortic stiffness, cognitive function, cardiac, retinal & renal microvascular damage and systemic inflammation.

Objectives:

1. Test whether MRI measures of cerebral small vessel disease in COPD is independent of cigarette smoking by comparing to age and smoking history matched controls.
2. Explore possible mechanistic relationships between MR measures of cerebral small vessel disease and perfusion in COPD with pulse wave velocity and markers of systemic inflammation.
3. Determine if MRI measures of cerebral small vessel disease and perfusion are associated with measures of microvascular damage in other susceptible organs (cardiac, retina and renal) in COPD.
4. Determine if MR measures of cerebral small vessel disease and perfusion in COPD are associated with cognitive function.
5. **STUDY DESIGN**

Prospective recruitment, to an observational case control study with cross-sectional analysis designed to compare 30 well-characterised COPD cases with 25 healthy smoker controls.

The broad timetable for the stages of the research

Preparation August 2013 - Dec 2013 (4 months)

Recruitment & Data Collection Jan 2014 - Jan 2015 (12 months)

Interpreting & analysing findings Feb 2015 - March 2015 (1 month)

Preparing the final report. April 2015 - May 2015 (1 month)

*Study visits will take place at the Respiratory Research Unit, North Bristol Lung Centre.

*Retinal imaging which will take place at north Bristol medical illustration and MRI which will take place at the Clinical Research imaging Centre (CRIC) Bristol 3T MRI scanner.

Recruitment will be from patients attending clinic at local University Teaching Hospitals. An age-matched control group will be recruited from the Bristol Primary care Research Network North Hub, local community either through local press advertisements or University non-healthcare staff. Controls will be excluded if they have any respiratory or memory difficulties.

All Participants will be invited for an MRI, retinal photography and 2 further study visits to undergo non-invasive assessment of aortic stiffness and collect the measures outlined below. The total duration of the study should be ~ 2½ hours.

**3.1 STUDY OUTCOME MEASURES**

**Primary outcome**

MRI: White Matter microstructural damage (Fractional Anisotropy)

**Secondary Outcomes**

1. Aortic Stiffness: Pulse Wave Velocity
2. MRI: Number of cerebral microbleeds (CMB)
3. MRI: Cerebral perfusion (Arterial Spin Labelling – ASL)
4. Cognitive Function (Montreal Cognitive Assessment – MoCA)
5. Systemic inflammation, (C reactive protein, Interleukin 6, Fibrinogen)
6. Cardiac MR (RV, LV mass, cardiac output)
7. Micro-albuminuria
8. Retinal arteriolar narrowing (arteriole to venule ratio)
9. Forced Expiratory Volume in 1 second (FEV1 % predicted)
10. Health Status
11. Arterial partial pressure of oxygen

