**Measures**

**3Tesla MRI:**

University of Bristol Clinical Research Imaging Centre (CRIC) [www.bristol.ac.uk/cricbristol](http://www.bristol.ac.uk/cricbristol)

*Summary Brain Imaging Protocol ~ 45min***.**

1. Anatomy / Volume
2. T1 FLAIR (Evidence of burden and pattern of vascular disease)
3. Diffusion Tensor Imaging (micro structure / evidence of recent ischaemia)
4. Resting Functional Imaging (marker of cerebral activity)
5. T2 Susceptibility weighted imaging (cerebral micro-bleeds)
6. Arterial Spin Labelling (measure of regional tissue perfusion

*Summary Cardiac Imaging Protocol ~ 20min*

1. Non-invasive imaging including fast gradient-echo cine images of the left and right ventricles.

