**Other demographic and disease severity measures:**

1) Detailed medical history

2) Arterialised earlobe capillary or radial artery blood gases whilst breathing room air

3) Blood pressure in resting state x 3

4) Vital signs including Oxygen saturation, Heart Rate, Respiratory rate

5) Health Status Questionnaire - COPD Assessment Test (CAT) .

6) Mood Questionnaire - Hospital Anxiety & Depression (HAD) questionnaire .

9) Spirometry: ATS/ ERS guidelines

10) Snellen chart (visual acuity)

11) Blood tests: Full Blood Count, Urea and Electrolytes, Fasting Glucose and Lipids

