**Healthy Ex-smoker Controls**:

Subjects must have a FEV1/FVC >70%;

Patient and control group will be matched for smoking history and age.

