**7. STATISTICS AND DATA ANALYSIS**

The proposed study analysis is, informed by past empirical evidence and scientific reasoning. It is designed to investigate potentially important differences in both brain pathology, and vascular function, between COPD and Smoker groups and to investigate associations between brain pathology and vascular function. Standard statistical techniques (independent sample t-test or nonparametric Mann Whitney test as appropriate and similar) will be used. In these respects a sample size of N = 55 will be taken with N = 30 sampled from the COPD population and with a comparator group of N = 25 from a smoker population. These sample sizes have been determined on feasibility and economic grounds and are comparable with past similar research . These studies showed very large effect sizes for a two-group comparison (Cohen’s d in excess of 1.0). For a conservatively estimated effect of d = 0.8, a sample of N = 30 compared against a sample of N = 25 will have in excess of 85% power (beta < 0.10) using alpha =0.05, two-sided.

- Data and all appropriate documentation will be stored for a minimum of 10 years after the completion of the study, including the follow-up period.

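### Secondary outcome 6 (cardiac MR) is named in unindexed quantities, with no weight listed, no matching on sex and unadjusted tests, so the cardiac comparison and Objective 3 lose precision and are open to confounding by sex and body size

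*Protocol*

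**What the plan says.** Five places in the Protocol bear on this point.

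- **Outcome.** Section 3.1, Secondary Outcomes, item 6: "Cardiac MR (RV, LV mass, cardiac output". Item 9 of the same list is on a standardised scale: "Forced Expiratory Volume in 1 second (FEV1 % predicted".
- **Acquisition.** The cardiac imaging summary under 3Tesla MRI gives "Non-invasive imaging including fast gradient-echo cine images of the left and right ventricles". No derivation or scaling rule follows.
- **Matching.** Section 4.2: "Patient and control group will be matched for smoking history and age". Objective 1 is the same: "by comparing to age and smoking history matched controls". Neither sex nor body size is named.
- **Analysis.** Section 7 names an "independent sample t-test or nonparametric Mann Whitney test as appropriate and similar". No covariate is mentioned. Objective 3 also uses the cardiac measures within the patient group, asking whether the cerebral MRI measures are "associated with measures of microvascular damage in other susceptible organs (cardiac, retina and renal) in COPD".
- **Data collected.** The list headed "Other demographic and disease severity measures" contains no weight, height, BMI or body surface area. Nor do the other measures in section 3.1 or the timed visit tables under Summary of investigations, treatment and assessments.

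**The concern.** LV mass and cardiac output are the usual names of the raw quantities. The versions scaled for body size are called mass index and cardiac index. Ventricular mass and cardiac output rise with body size and are, on average, larger in men. If the raw values are compared between groups not matched on sex or size, three things follow.

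- Variation due to sex and size adds to the error term and lowers power, even when the groups are balanced.
- A chance or recruitment-driven imbalance in sex or size can create or hide a COPD difference. If patients with COPD weigh less than controls, for example, increased mass could be masked.
- Matching patients to controls gives no protection in Objective 3. That analysis runs within about 30 patients, whose sex and size vary freely and enter the raw cardiac value directly.

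The data-collection side belongs in the protocol. An analysis plan can choose an index or an adjustment, but it cannot supply a body weight that was never recorded.

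**Working it through.** The Protocol states no figure for cardiac MR, so there is none to reproduce. The calculation shows how large the effect could be.

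**Inputs from the Protocol (section 7).** 30 COPD and 25 controls; alpha 0.05, two-sided.

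**Assumptions, not in the Protocol.** Sex difference in LV mass D = 30-40 g; within-sex SD s = 20-25 g; half of participants male; true COPD difference 15 g.

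**Step 1. Share of variance due to sex.** With half male, the between-sex variance is 0.25 × D². Total SD = √(s² + 0.25·D²) and share = 0.25·D² / (s² + 0.25·D²).

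**Step 2. Power for 15 g.** Noncentral t with 53 degrees of freedom and noncentrality (15/SD) × √(30·25/55). SD is the total SD for raw mass, and s if the sex component is fully removed.

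| D (g) | s (g) | Total SD (g) | Share due to sex | Power, raw | Power, sex part removed |
|---|---|---|---|---|---|
| 30 | 20 | √(400 + 225) = 25.0 | 225/625 = 36% | 59% | 78% |
| 30 | 25 | √(625 + 225) = 29.2 | 225/850 = 26% | 46% | 59% |
| 40 | 20 | √(400 + 400) = 28.3 | 400/800 = 50% | 49% | 78% |
| 40 | 25 | √(625 + 400) = 32.0 | 400/1025 = 39% | 40% | 59% |

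The last column shows what complete removal of the sex component would give, as by adjustment for sex. It is not an estimate of what dividing by body surface area would achieve.

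**Step 3. Chance imbalance without matching on sex.** SD of the difference in male share = √(0.25/30 + 0.25/25) = 0.135, or 13.5 percentage points. With exact binomials and 50% male in both source populations, the probability of a gap of at least 15 points is 27%, of at least 20 points 15%, and of at least 30 points 3%.

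**Step 4. Effect of a gap.** Shift in the group contrast = gap × D. The smallest is 0.15 × 30 = 4.5 g and the largest is 0.20 × 40 = 8 g, about 0.15 to 0.28 of a total SD. With a 20-point gap and no true COPD effect, a nominal 5% test rejects 10.0%, 14.2% or 17.9% of the time when the sex difference is 1.0, 1.5 or 2.0 within-sex SDs. A weaker sex effect of 0.5 SD gives 6.4%.

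Nothing here quantifies RV mass, cardiac output, or body size within sex. The figures concern LV mass and sex only.

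**The case against.** The strongest reply is that the finding reads too much into a one-line list entry. The Protocol never says the values are absolute, and indexing or covariate adjustment may be set out in an analysis plan that is not at hand. Section 7 also ends its list of tests with an open phrase. This stands in part: the choice of scale could be fixed later. But the names used are those of the unindexed quantities, and that route does not help if weight is not collected.

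Second, the list of other measures jumps from item 6 to item 9, so two entries may have been lost, and it names neither age nor sex, so it is not exhaustive. That is fair: absence from this list does not prove that weight goes unrecorded. The visit tables are a separate listing, itemised down to a two-minute dipstick, and they show no anthropometry either.

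Third, FEV1 % predicted needs sex and height, so both are implicitly recorded. This stands. Adjustment for sex and a height-indexed version are already possible; only indexing by body surface area depends on weight.

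A reader might go further and infer that the cardiac outcomes largely measure sex and body size. The documents do not support that. They contain no figure on it, and under the assumptions above sex explains at most half of LV mass variance. Nor does the Protocol set a scoring direction under which a large healthy man would count as damaged. Section 1.1 links emphysema and lung function to lower cardiac output, so on that measure he would look less impaired.

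**Conclusion.** The point holds as one about precision and exposure to confounding. As written, outcome 6 is in unindexed quantities, no weight is listed, matching omits sex and size, and the named tests are unadjusted. Under the assumed values, sex accounts for about 26-50% of LV mass variance, and leaving it in costs roughly 12 to 29 percentage points of power for a 15 g difference (59% − 46% unrounded is 12; 78% − 49% is 29). A false group difference also requires an actual imbalance in sex or size, which is possible (15% chance of at least 20 points) but not established.

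All gram values and the sex mix are assumptions. The scope is one of eleven secondary outcomes plus the cardiac part of Objective 3. The primary outcome and its power statement are not affected. This is a worthwhile, inexpensive improvement rather than a fault that threatens the study.

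**What to change.** - List height and weight among the measures, taken at visit 1, and add them to the visit table.
- In section 3.1, define outcome 6 as LV mass index, RV mass index and cardiac index (each divided by body surface area), with a height-indexed version as a sensitivity analysis.
- State in section 7 that the cardiac group comparison and the cardiac associations under Objective 3 are adjusted for sex.

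The cost is about one minute per participant and a change of wording. The drawback is that indexing by body surface area can over-correct in underweight participants, which is the reason for the height-indexed sensitivity analysis. If weight turns out to be recorded already, only the wording changes.

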**Retinal Photography:**

Non-mydratic, macular focused retinal photography will be collected by qualified technicians with the study site department of medical illustration. Generalised retinal arteriolar narrowing will be estimated by measuring retinal vessel diameters from photographs by use of validated imaging software. Reproducibility from photographs is excellent (kappa 0.80 – 0.99) (22).

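### Secondary outcome 8 equates retinal arteriolar narrowing with the arteriole-to-venule ratio, which alone cannot tell arteriolar narrowing from venular widening

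*Protocol*

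**What the plan says.** Protocol section 3.1, Secondary Outcomes, item 8, reads "Retinal arteriolar narrowing (arteriole to venule ratio"). No other retinal metric appears in the list of 11 secondary outcomes.

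The Retinal Photography paragraph under Measures uses the same construct and says how the data arise: "Generalised retinal arteriolar narrowing will be estimated by measuring retinal vessel diameters from photographs by use of validated imaging software". It does not say that arteriolar and venular calibres will each be reported or analysed.

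The outcome serves Objective 3, which asks whether the cerebral MRI measures are "associated with measures of microvascular damage in other susceptible organs (cardiac, retina and renal) in COPD". The rationale in section 1.1 is similarly broad: "Retinal photography is a sensitive and precise method of assessing retinal microvascular signs". Neither statement is confined to arterioles.

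**The concern.** The outcome's name and its metric do not match. Arteriolar narrowing is a statement about one vessel type; the ratio depends on two. Whatever the ratio shows, a group difference or a correlation with an MRI measure, will be reported under a heading that assigns it to arterioles, although the reported quantity cannot support that assignment. In the other direction, if arterioles and venules narrowed together, the ratio would show nothing.

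At stake is the interpretation of one secondary outcome and of the retinal part of Objective 3. The protocol itself fixes both the label and the metric.

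**Working it through.** **Inputs.** The construct and metric come from Secondary Outcomes item 8; the acquisition of vessel diameters comes from the Retinal Photography paragraph. The protocol gives no ratio value, standard deviation or expected retinal effect, so there is no stated figure to reproduce. The percentage changes below are assumed, for illustration only.

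**Formula.** Let A be arteriolar and V venular diameter, so the ratio is A/V. If A changes by a fraction a and V by a fraction v, the relative change in the ratio is (1 + a)/(1 + v) − 1.

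| Scenario | Calculation | Change in ratio |
| --- | --- | --- |
| Arterioles 5% narrower, venules unchanged | 0.95/1 − 1 | −5.0% |
| Arterioles unchanged, venules 5% wider | 1/1.05 − 1 | −4.8% |
| Both 5% narrower | 0.95/0.95 − 1 | 0.0% |
| Arterioles 3% narrower, venules 3% wider | 0.97/1.03 − 1 | −5.8% |

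**Range.** For changes of 2%, 5% and 10%:

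- arteriolar narrowing lowers the ratio by 2.0%, 5.0% and 10.0%;
- venular widening lowers it by 1.96%, 4.76% and 9.09%.

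The two are close but not identical. The venular widening that reproduces the arteriolar effect exactly is 1/(1 − x) − 1, which gives 2.04%, 5.26% and 11.1%.

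**Group comparison.** On the log scale, log(A/V) = log A − log V. The between-group difference in mean log ratio is the difference in mean log A minus the difference in mean log V. That is one number for two unknowns, so the ratio alone does not identify the arteriolar part.

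**Association (Objective 3).** For any MRI measure X, cov(log(A/V), X) = cov(log A, X) − cov(log V, X). A correlation with the ratio may come from either term, and equal terms cancel.

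**What the ratio does well.** If a scale error k, such as image magnification, multiplies both diameters, then kA/kV = A/V and the error disappears. An absolute diameter carries it in full: a 5% magnification error shifts A and V by 5% each and the ratio by 0%.

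**The case against.** The strongest reply is that the ratio is a reasonable choice for a broad aim. Objective 3 concerns retinal microvascular damage in general, and a ratio that responds to either vessel type can serve it. The ratio also removes common magnification error; the protocol lists a Snellen chart but no refraction or axial length from which absolute diameters could be corrected. Vessel diameters are to be measured anyway, and separate tabulation might be set out in an analysis plan that is not shown. Most of this stands. It argues for keeping the ratio and against any claim that data are lost. It does not repair the label: the protocol names an arteriolar construct and attaches a metric that is not specific to arterioles. A broad microvascular aim would also want to detect parallel narrowing of both vessel types, which the ratio misses.

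Two stronger readings are tempting, and the protocol supports neither.

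- A reader might infer that the outcome cannot show arteriolar damage at all. It can: the ratio falls 5.0% when arterioles narrow by 5% and venules do not change. The defect is lack of specificity, together with blindness to proportional change in both.
- A reader might infer that venules are expected to differ between the groups because of inflammation, hypoxia or smoking. Section 1.1 lists systemic inflammation and "physiological stress (hypoxia, sympathetic nervous system activation") among mechanisms of vascular disease in COPD, but nowhere mentions retinal venules. The groups are to be matched on smoking history, and resting saturation below 92% and long-term oxygen therapy are exclusions. These do not rule out a venular difference, but nothing in the protocol establishes one.

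**Conclusion.** The point holds as a mismatch between label and metric. The ratio alone cannot separate arteriolar narrowing from venular widening (−5.0% against −4.8% for illustrative 5% changes) and does not change when both vessel types narrow in proportion. This follows from the definition of a ratio and needs no clinical assumption.

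The size of any misattribution in this study is unknown. It would depend on how far venular calibre differs between the groups, or varies with the MRI measures, and the protocol gives no figure for either. The effect is limited to the reading of one of 11 secondary outcomes and the retinal part of Objective 3. The primary outcome (fractional anisotropy) and the planned 30 and 25 participants are unaffected. This is a minor to moderate point, worth acting on because the correction is cheap.

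The reproducibility statement in the Retinal Photography paragraph (a kappa range and its citation) is a separate editorial matter. The conclusion here does not rest on it.

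**What to change.** Relabel outcome 8 as retinal vessel calibre: arteriole-to-venule ratio, with summary arteriolar and venular diameters reported and analysed separately from the same photographs. Use matching wording in the Retinal Photography paragraph. State that arteriolar narrowing will be concluded only when the arteriolar diameter itself supports it. Keep the ratio, because it cancels a scale error common to both vessels, and read the three results together.

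Cost: a change of wording and one or two extra secondary variables, with slightly more multiplicity among the secondary results. No new procedure, visit or participant is needed. The absolute diameters are exposed to magnification error, and the report should say so.
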